## 6.6 Laboratory Testing

Using standard techniques, laboratory testing will be performed by the certified Clinical Laboratory.

1. Full blood count, including white blood cell differential
2. Serum creatinine
3. AST and ALT, Creatinine Phosphokinase (CPK)
4. HIV and Hepatitis B sAg, Hepatitis C Antibody test
5. hCG (Females only)
6. Urinalysis (in the event of an abnormal urine dipstick test full microurine tests will be undertaken)

Urine β-hCG testing will be performed at the clinical trial site using an approved urine pregnancy test kit. Urinalysis will be tested by urine dipstick testing at the trial site using an approved product. Microscopic examination will be undertaken only in the case of clinically significant abnormality by dipstick.

## 6.7 Immunologic Testing

Immunology studies will be performed at the three locations:

WEHI, [name]’s Laboratory – antibody reactivity (ELISA, immunofluorescence, Western blots) and growth inhibition assays using dialysed serum.

NIH, [name]’s Laboratory – Growth inhibition assays using purified IgG.

QIMR/QHPS - Cellular Immunology

Blood samples collected from participants will be processed and aliquoted according to specific laboratory instructions. The trial site will securely store all serum/plasma samples at -80ºC until shipment. Frozen sera/plasma will be shipped to the Laboratories on dry ice in batches. An inventory of each shipment will be maintained by both the trial site and the analysing Laboratory. Peripheral Blood Mononuclear Cells (PBMC) will be prepared according to the analytical laboratory procedures and transferred to the laboratory for assay preparation.

### 6.7.1 Antibody Assays

### 6.7.1.1 Enzyme Immunoassays (ELISA)

Antibody levels to the MSP2 antigens will be measured in serum by ELISA using established protocols. The MSP2 antigens for these assays will be provided by CSL Limited. Each sample will be tested in duplicate against 3D7 and FC27 MSP2 alleles. A titration of a reference positive control serum will be included in every assay. Total IgG, IgM and IgG isotypes will be measured. In addition to MSP2-3D7 and MSP2-FC27, serum samples may also be tested against MSP2 proteins with other sequences.

### 6.7.1.2 Immunofluorescence microscopy

A selection of samples that were found to be positive to MSP2 by ELISA will be tested for reactivity to the surface of merozoites using confocal immunofluorescence microscopy. *In vitro* cultures of *P. falciparum*-infected erythrocytes at the schizont stage will be smeared on glass slides, fixed, and probed with ELISA-positive serum from vaccinnees and from recipients of ISA720 Control.

### 6.7.2 Western blotting of parasite protein extracts

A selection of positive serum samples, and serum from participants receiving ISA720 Control vaccine, will be tested for immunoreactivity of MSP2 in protein extracts of *P. falciparum* by Western blot. *P. falciparum*-infected erythrocytes at the schizont stage and a protein extract prepared using established procedures. The protein extract containing MSP2 will be run on a SDS-PAGE gel followed by Western transfer and blotting with serum samples. Rabbit antibodies raised against MSP2 will act as a positive control.

### Growth Inhibition Assay

The GIA is designed to determine whether anti-MSP2 antibodies obtained from a vaccinee can inhibit merozoite invasion of red cells. This will be performed using two different established approaches, in [name]’s laboratory, NIH (MVI-supported GIA Reference Center), and [name]’s Laboratory, WEHI (34).

Synchronized mature blood-stage parasites from the 3D7 and FC27 lines are incubated with purified IgG ([name] Laboratory) or dialysed serum ([name] Laboratory) from volunteer sera *in vitro*. The number of infected red cells will be determined by assaying parasite lactate dehydrogenase activity ([name] Laboratory) or by flow cytometry ([name] Laboratory). Growth inhibitory activity is defined as the percentage reduction in the number of newly invaded red cells (determined by parasitemia) by post vaccination serum/IgG compared to serum/purified IgG from Day 0 samples or samples from recipients of the ISA720 Control. In addition to 3D7 and FC27, serum samples may also be tested against parasites expressing MSP2 with other sequences

### Cell Mediated Immunity (CMI)

T-Cell Proliferation and cytokine response

The T-cell proliferation will define the cellular immune response to the vaccine candidate. The assay involves *in vitro* culture of PBMC with vaccine antigen and appropriate controls. T-Cell proliferation and cytokine responses will be described in the Laboratory Reference methods.

## 6.8 Use, Storage, and Tracking of Specimens and Data

Immunological samples and data collected under this protocol will be used to study malaria and possible adverse reactions to vaccination. No genetic testing will be performed. Access to research samples will be limited using either a locked room or a locked freezer. Samples and data will be stored using codes assigned by the investigators or their designees. Data will be kept in password-protected computers. Only investigators or their designees will have access to the samples and data.

Aliquots of serum/plasma samples will be stored at both QIMR and WEHI. Samples will be tracked using sample logs. The research use of stored, unlinked, or unidentified samples may be exempt from the need for prospective HREC/IRB review and approval. Exemption requests will be submitted in writing to the relevant Human Research Ethics Committees authorised to determine whether a research activity is exempt.

Participants may decide at any point not to permit their samples to be stored. In this case, the principal investigator or the laboratory nominee will destroy all known remaining samples and report what was done to both the subject and to the IRB/HREC’s. This decision will not affect the subject’s participation in this protocol or any other protocols.

# 7.0 Adverse Events Monitoring and Reporting

## 7.1 Definitions

### 7.1.1 Adverse Event (AE)

An adverse event (AE) includes any noxious, pathological, or unintended change in anatomical, physiological or metabolic functions as indicated by physical signs, symptoms and/or laboratory-detected changes occurring in any phase of the clinical study, whether associated with the study vaccine or ISA720 Control, and whether or not considered vaccination related. This includes an exacerbation of pre-existing conditions and intercurrent illnesses. Unchanged pre-existing conditions will not be included as an adverse event. All AEs must be graded for intensity and relationship to the investigational vaccine as described in **Sections 7.2.2** and **7.2.3**.

### 7.1.2 Serious Adverse Event (SAE)

An SAE is an AE, whether considered related to the investigational vaccine or not, meeting one of the following conditions:

1. Death during the period of protocol-defined surveillance.
2. Life threatening: defined as an event that places a subject at immediate risk of death at the time of the event and does not refer to an event that hypothetically might have caused death were it more severe.
3. Hospitalisation during the period of protocol-defined surveillance: defined as at least an overnight stay in the hospital or emergency ward for treatment that would have been inappropriate if administered in the outpatient setting.
4. Results in a congenital anomaly or birth defect.
5. Results in a persistent or significant disability or incapacity: defined as a substantial disruption of the study participant’s ability to carry out normal life functions.
6. Any other important medical event that may not result in death, be life threatening, or require hospitalization, may be considered a serious AE when, based upon appropriate medical judgment, the event may jeopardize the subject and may require medical or surgical intervention to prevent one of the outcomes listed above.

## 7.2 Assessment of Adverse Events

### 7.2.1 Identification of AEs

Assessment of safety will include clinical observation and monitoring of hematological, chemical and immunologic parameters. Safety will be evaluated by monitoring of volunteers for local and systemic adverse reactions during the course of the trial. Volunteers will be closely observed in the clinic for approximately 30 minutes after each vaccination and contacted by telephone on Day 1 and 21 after each vaccination to inquire about reactions. Additionally, volunteers will return to the clinic on Days 3, 7, 14 and 28 following each vaccination for clinical assessments. Clinical staff must accurately measure the total affected area of any volunteer presenting with erthyema, swelling and induration with a ruler or tape measure. Measurement must be documented at each visit until resolution. Clinical staff may elect to photograph injection site reactions over time for any volunteer. Clinical staff must apply the Brighton’s Collaboration Assessment Tool on any nodules or suspected nodules or to differentiate induration from a nodule.

For 13 days after each immunisation, volunteers will be asked to keep daily diaries of symptoms, recording oral temperature, as well as a subjective assessment of the extent of induration, erythema, pain/ tenderness at the site of injection, and any systemic signs and symptoms. The size of any injection-site reaction will be measured using a standardized clear plastic measurement device and recorded in the volunteer symptom diary. A third diary card will be given at the 14 day visit following each vaccination for the volunteer to record only injection site reactions. (Days 14-28).

At each clinic visit to Day 28, clinic staff will review the volunteer diaries, confirm the symptoms experienced and record AEs as appropriate in the source document. Individual symptom reports of pain, tenderness and muscle ache at injection site will be recorded as the AE term of pain at injection site.

All AEs will be graded for intensity and relationship to study product. Reactions will be graded as described in **Appendix 2** in this protocol. A study clinician will be available by telephone or pager 24 hours a day during the study evaluation period. Should a volunteer call a study clinician to report an adverse event, it will be determined at that time if an extra visit(s) will be scheduled, and/or appropriate medical advice will be provided. Additionally, all calls will be documented in the volunteer’s study chart, and discussed with the Principal Investigators.

All local and systemic reactions not meeting the criteria for “serious adverse events” will be captured on the appropriate case report form (CRF). These events will be followed to adequate resolution.

### 7.2.2 Determination of Severity

Severity of AEs will be assessed by the investigator as described in **Appendices 2, 3, and 4**. AEs not included in **Appendices 3 and 4** will be graded for severity using the following definitions:

Grade 0 (None):

Grade 1 (Mild): No effect on activities of daily living.

Grade 2 (Moderate): Partial limitation in activities of daily living (can complete  50% of baseline), or treatment given.

Grade 3 (Severe): Activities of daily living limited to < 50% of baseline, or medical evaluation required.

Grade 4 (Life- Extreme limitation in activity, significant assistance required;

threatening): immediate medical intervention or therapy required to prevent death.

Grade 5: Death.

Intensity of solicited AEs will be assessed by the investigator as described in **Appendix 2.** All laboratory AEs will be graded in severity following the toxicity table in **Appendix 3**. Unexpected adverse events not described in the protocol will be graded according to the common toxicity table in **Appendix 4**.

The maximum observed intensity reported for any AE is recorded for the entire duration of the AE.

### 7.2.3 Association with Receipt of the Study Vaccine

All AEs will have their possible relationship to study vaccine assessed using the following definitions:

Definite: Clear-cut temporal association, and no other possible cause.

Probable: Clear-cut temporal association and a potential alternative etiology is not apparent.

Possible: Less clear temporal association; other etiologies also possible.

Unlikely: Temporal association between the AE and the vaccine or the nature of the event is such that the vaccine is not likely to have had any reasonable association with the observed illness/event (cause and effect relationship improbable but not impossible).

Not Related: The AE is completely independent of vaccine administration; and/or evidence exists that the event is definitely related to another etiology.

The degree of certainty with which an AE can be attributed to administration of the study vaccine will be determined by how well the event can be understood in terms of one or more of the following:

1. The event being temporally related with vaccination or reproduced on re-vaccination.
2. A reaction of similar nature having previously been observed with this type of vaccine and/or formulation.
3. The event having often been reported in the literature for similar types of vaccines.

All local (injection-site) reactions will be considered causally related to vaccination.

## 7.3 Adverse Event Reporting

All SAEs will be reviewed by a study physician, recorded on the appropriate SAE form, and followed through to resolution by a study physician. All SAEs will be reported by telephone, fax, or email within 1 working day of notification of the SAE occurrence to all of the following:

- Queensland Institute of Medical Research-Human Research Ethics committee
  (QIMR-HREC): [contact], [contact].
- Western Institutional Review Board (WIRB®): PATH-MVI will report adverse events to WIRB.
- WEHI Walter and Eliza Hall Institute – Human Research Ethics Committee, [name].

Following notification from the Principal Investigators, the sponsor (QIMR), will report events that are both serious and/or unexpected that are possibly, probably or definitely related to the vaccine, to the TGA within the required timelines: fatal and life-threatening events within 7 calendar days (by phone or fax) and all other SAEs in writing within 15 calendar days. In addition, the Principal Investigators will notify the QIMR nominated CRO monitor within 1 working day of notification of the SAE occurrence, who will in turn notify MVI. MVI will then notify the WIRB.

- Australian TGA Sponsor (Queensland Institute of Medical Research [QIMR]):
  [contact], [contact]
- Funding Sponsor (PATH-MVI): [contact], [contact] or by Email: [contact]

All SAEs not listed as possibly, probably or definitely related will be reported to the IRB/ HREC at least annually in a summary format as required by the institution. All local and systemic reactions not meeting the criteria for “serious adverse events” will be captured on the appropriate case report form (CRF). These events will be followed to resolution or stablisation. (Allow for 30 days after last study visit /or conclusion of the study.

## 7.4 Adverse Event Monitoring

### 7.4.1 Local Medical Monitor

An independent local Medical Monitor has been appointed for oversight of safety in this trial. The local Medical monitor will be available to advise the investigators on trial-related medical questions or problems, and act as a representative for the volunteers’ welfare. Additionally, the local Medical Monitor may ask to convene a safety monitoring committee (SMC) meeting for review of any safety issue or adverse event. The Medical Monitor will review all SAEs.

### 7.4.2 Safety Monitoring Committee

The sponsor (QIMR) in consultation with MVI will select three independent monitors to form the Safety Monitoring Committee to advise the site and the study investigators on the trial safety. The SMC will be independent of sponsors and the clinical trial site. The SMC’s primary responsibility will be to monitor volunteer safety. The SMC will meet at the nominated schedule (Table 1) following the immunizations of the 10 µg and 40 µg dose groups to approve further vaccination in selected cohorts and dose escalation, and whenever the need should arise. The SMC will review cumulative safety data for evidence of study-related AEs, adherence to the protocol, and factors that may affect outcome or study data such as protocol violations and losses to follow-up. At each meeting the SMC will make a recommendation regarding the safe continuation of the study. If no stopping criteria are met (**Section 7.5**), with the approval from the SMC the trial will proceed.

The Principal Investigators are responsible for ensuring that the SMC is aware of all new safety information.

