## 1.2 Secondary Objectives

### 1.2.1. Characterise the humoral and cellular immune responses to the MSP2-C1/ISA720 vaccine

### Determine the vaccine dose level that induces the highest serum IgG concentration to MSP2 by ELISA

Table 1: MSP2-C1/ISA720 Vaccine Dose Escalation Schedule

| Time  (Week) | Cohort 1: (n = 15) | Cohort 2: (n = 15) |
| --- | --- | --- |
| 10 μg MSP2-C1/ISA720 | 40 μg MSP2-C1/ISA720 |
| 0 | Vaccination 1 (n=15) |  |
| 4 |  | Vaccination 1 (n=5) |
| 8 |  | Vaccination 1 (n=10) |
| 11 | SMC | SMC |
| 12 | Vaccination 2 (n=15) |  |
| 13 |  |  |
| 16 |  | Vaccination 2 (n=5) |
| 17 |  |  |
| 20 |  | Vaccination 2 (n=10) |
| 24 | Vaccination 3 (n=15) | SMC |
| 25 |  |  |
| 28 |  | Vaccination 3 (n=5) |
| 29 |  |  |
| 32 |  | Vaccination 3 (n=10) |
| 36 |  | SMC |
| 37 |  |  |
| 41 |  |  |
| 48 | Last Visit |  |
| 52 |  | Last visit (n=5) |
| 56 |  | Last visit (n=10) |

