**** Table 1- Timing of vaccinations shown as a minimum. First Vaccinations may be delayed.**

# 2.0 Introduction

## 2.1 Background

The World Health Organisation reported in 2005 that malaria kills more than 1 million people annually and that approximately 3.2 million people living in 107 countries or territories are at risk of infection [1]. Most of the malaria mortality occurs in sub‑Saharan Africa and in children under 5 years of age. Of the four species of malaria parasite that infect humans, *Plasmodium falciparum* is responsible for the majority of these deaths. Mounting drug resistance of the malaria parasite, as well as widespread resistance of mosquitoes to insecticides, make these control strategies increasingly unrealistic. A vaccine that would reduce both mortality and morbidity secondary to *P. falciparum* infection would be a valuable resource in the fight against this disease.

*P. falciparum* has a complex life cycle. Sporozoites, the infectious stage of the parasite, are transmitted to humans through the saliva of infected female mosquitoes while taking a blood meal. Sporozoites travel through the bloodstream to the liver, where they invade hepatocytes and then multiply asexually into merozoites. Six to 10 days after invasion, the hepatocytes rupture, releasing thousands of merozoites into the bloodstream. These merozoites invade erythrocytes, multiply and after 2 days, release progeny merozoites, which subsequently invade new erythrocytes to continue the asexual blood-stage cycle. Clinical symptoms in humans are due to this asexual blood-stage of the parasite’s life cycle. A small percentage of merozoites do not multiply after invading erythrocytes, but instead differentiate into gametocytes. These gametocytes are ingested by a female mosquito during a subsequent blood meal and undergo sexual reproduction in the mosquito midgut, producing a zygote. The zygote matures and releases sporozoites that migrate to the mosquito’s salivary glands, thus completing the life cycle.

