The most common adverse event observed in trials using Montanide ISA720 is local reactogenicity (34). The acute reactions are characterized by of pain, swelling, induration, sterile abscess, and granuloma formation. These have been generally mild to moderate in 33 to 91% of volunteers. In the single Phase 2 trial in children in an endemic area the rate was 12% (26). The overall rate for mild and moderate acute local reactions is similar to that observed with licensed pediatric vaccines such as DT (standard pediatric dose) (55% mild/moderate local reactions) or dT (low dose vaccine) (52% mild/moderate reactions) in 6-year-old children. Severe local reactions occurred only with 5 vaccinees who received the vaccine via the intramuscular route for a cumulative rate of 1%. This proportion is not greater than that observed for some licensed vaccines (17% severe local reactions with DT and 11% severe local reactions with dT) (35). Severe local reactions were seen much more commonly in trials administering the vaccine subcutaneously. In these 2 trials (30) up to 44% of recipients of higher doses were not revaccinated due to local reactions. Acute local reactions were seen frequently with pain, swelling and/or induration most common. In the HIV vaccine study (33) sterile abscess and granuloma formation was seen in some volunteers, particularly those receiving the high antigen dose (2 mg), which was far in excess of that given in the malaria vaccine studies or that planned in this study. In most studies the vaccine was injected intramuscularly and when this route was used the majority of local reactions were mild to moderate with a cumulative rate of 1% for severe reactions. In contrast, severe local reactions were seen more commonly in the two studies in which the vaccine was administered subcutaneously (31, 32).

Delayed local reactions as seen in the Combination B studies (see Section 2.3.2) occurred in some volunteers in the majority of other trials with antigens formulated in Montanide® ISA720. Over all of the studies approximately 11% of volunteers developed these reactions, which were characterized by pain and swelling at the injection site occurring 10-28 days after vaccination. They resolved without sequelae usually in a few days but in some cases several weeks. There was a trend indicating that the rate and severity of these delayed reactions was increased with higher antigen doses and multiple injections.

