Thirty volunteers will be enrolled and assigned to one of two dose groups (10 or 40µg) or ISA720 Control as outlined in **Table 1**. All vaccines and the ISA720 Control will contain the same amount of Montanide® ISA720. As with other recombinant protein vaccines, hypersensitivity reactions would be expected to occur within the first 24 hours after receipt of the vaccine, and other severe local or systemic reactions within 72 hours. As outlined above, delayed local reactions have been observed in previous ISA720 vaccine studies. Thus, volunteers will be reviewed on days 3, 7, 14 and 28 following each vaccination, and vaccinations will be staggered within the higher dose cohort such that 5 volunteers will be vaccinated 4 weeks prior to the remaining 10 volunteers. Stopping rules as detailed in **Section 7.5** below will be in place to enable suspending the trial until review by the safety monitoring committee (SMC).

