## 3.2 Sample Size and Estimated Duration of Study

A total of 30 volunteers will be vaccinated in 2 cohorts of 15 (see **Section 9.1.4** for a justification of the sample size). Twelve in each cohort will be randomized to receive 10 or 40 µg of MSP2-C1 formulated in ISA720; 3 in each cohort will be randomized to receive ISA720 Control. The trial is expected to last for a total of 56 weeks. Each volunteer will be followed for 48 weeks from the time of the first injection.

It is estimated that up to 150 volunteers will need to be screened to complete enrolment.

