## 3.3 Group Allocation, Randomisation and Blinding

The two dose groups will be screened and enrolled consecutively. Once screening has started and the first 15 participants have been deemed eligible, they will be assigned to Cohort 1 and a Day 0 visit will be scheduled. Alternates may also be identified and held in reserve. The first dose group will be vaccinated over the course of 1-2 days, with 2 participants completed a day prior to the remaining 13. If the alternates are not vaccinated, they will be invited to participate as members of the second cohort. The second dose cohort will be split into 2 subgroups for vaccination. The first 5 participants of the 40 µg dose cohort will be vaccinated at least 4 weeks after the last vaccination of the previous dose cohort and the remaining 10 participants in this dose cohort will be vaccinated at least 4 weeks after the first 4 participants in their cohort to maximize safety. After the first vaccination for each dose cohort, no replacement volunteers will be added if a subject withdraws from the study.

In this trial, everyone will be blinded to the randomisation scheme except for the study pharmacist (or designee) who prepares the vaccine dose for administration. Randomization and blinding occur within each dose cohort. The study pharmacist/nominee will prepare identical syringes containing the study vaccines, according to a randomisation schedule provided by the study statistician, so that personnel who perform the study assessments do not know the identity of the study vaccine. Each participant considered eligible for vaccination will be assigned a randomisation number at Visit 1 (Day 0) (Section 6.4). The randomization number will used to identify the participant throughout the remainder of the study.

The volume of vaccine and ISA720 Control will be identical for each group. The study pharmacist will provide the person administering vaccine with the subject’s randomisation number, initials, and a blinded syringe containing the study medication. The pharmacist (or designee) will not inform any of the investigational staff of the treatment assignment and will not perform any other subject-related duties.

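### The SMC is to approve dose escalation at its Table 1 meetings, but at Table 1's minimum timing none of them precedes the only escalation step, from 10 µg to 40 µg

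*Protocol*

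**What the plan says.** Four places in the protocol bear on who releases the 40 µg dose.

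- **Section 7.4.2** ties the committee's meetings to a calendar: "The SMC will meet at the nominated schedule (Table 1) following the immunizations of the" 10 µg and 40 µg groups. It gives their purpose as "to approve further vaccination in selected cohorts and dose escalation, and whenever the need should arise". If no stopping criterion is met, the trial goes on with the committee's approval.
- **Table 1** (under Section 1.2) lists SMC meetings at Weeks 11, 24 and 36 only. Cohort 1 receives 10 µg from Week 0. Cohort 2 receives its first 40 µg injection at Week 4 (n=5), and the entry for the rest, "Vaccination 1 (n=10"), stands at Week 8. The note under the table reads "Timing of vaccinations shown as a minimum. First Vaccinations may be delayed".
- **Section 3.3** says that the first five of cohort 2 "will be vaccinated at least 4 weeks after the last vaccination of the previous dose cohort", with the other ten at least 4 weeks later. It does not mention the SMC.
- **Section 3.1** describes the same stagger ("5 volunteers will be vaccinated 4 weeks prior to the remaining 10 volunteers") and relies on the Section 7.5 stopping rules to suspend the trial pending SMC review.

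**The concern.** A dose-escalation approval is useful only if it comes before the higher dose. Section 7.4.2 gives that approval to the scheduled meetings, yet the schedule it cites holds no meeting between the start of 10 µg and the start of 40 µg. Once cohort 2 has begun there is no higher dose left to approve.

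The site could follow Table 1 and the Section 3.3 interval and start 40 µg after four weeks with no hold in force. An ethics committee that relied on Section 7.4.2 would expect the SMC to have approved the step first.

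Section 2.3.2 says that this formulation has not been tested in humans. It also reports that delayed local reactions in the Combination B trials rose with antigen dose. Section 2.3.3 describes such reactions as "pain and swelling at the injection site occurring 10-28 days after vaccination". The data that matter most for the step therefore arrive late in cohort 1's first month, and a planned look at them is what the approval clause appears to promise.

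No endpoint, estimate or sample size is affected.

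**Working it through.** This is a calendar check.

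**Inputs.**
- SMC meetings: Weeks 11, 24, 36 (Table 1).
- Cohort 1 injections: Weeks 0, 12, 24, n=15 each (Table 1).
- Cohort 2 injections: dose 1 at Weeks 4 (n=5) and 8 (n=10), dose 2 at Weeks 16 and 20, dose 3 at Weeks 28 and 32 (Table 1).
- Allocation in each cohort: 12 active, 3 control (Section 3.2).
- Follow-up: 48 weeks from first injection (Section 3.2).
- Day 28 visit window: ±5 days (Section 6.4).

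**Step 1: reproduce the plan's dates.** Applying the Section 3.3 intervals to a Week 0 start gives 0 + 4 = Week 4 for the lead five and 4 + 4 = Week 8 for the other ten. Last visits are 0 + 48 = Week 48, 4 + 48 = Week 52 and 8 + 48 = Week 56. All match Table 1 and the stated duration ("The trial is expected to last for a total of 56 weeks").

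**Step 2: set each meeting against the injections.**

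| SMC meeting | Injections listed for later weeks | Can it gate the first 40 µg dose? |
|---|---|---|
| Week 11 | Dose 2 (Weeks 12, 16, 20) and dose 3 (Weeks 24, 28, 32) | No, given at Weeks 4 and 8 |
| Week 24 | Cohort 2 dose 3 (Weeks 28, 32) | No |
| Week 36 | None; last injection is Week 32 | No |

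Meetings before Week 4: 0 of 3. Meetings before Week 8: 0 of 3. The further-vaccination half of Section 7.4.2 works, because Week 11 precedes every second dose. The dose-escalation half does not.

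**Step 3: size.** First injections in cohort 2 before any scheduled meeting: 5 + 10 = 15, of which 12 are active. Planned 40 µg injections number 12 × 3 = 36, so 12 of 36 can precede the first scheduled review. The lead group is injected 11 − 4 = 7 weeks before it and the rest 11 − 8 = 3 weeks before it. These figures count exposure before a scheduled meeting. They do not count unmonitored exposure.

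**Step 4: does the four-week interval at least secure the cohort 1 data?** Not fully. The Day 28 visit can fall on Days 23 to 33, and the Days 14-27 diary card is collected there. At minimum timing 40 µg starts on Day 28, up to 33 − 28 = 5 days before the last of those visits.

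**Step 5: does delaying cohort 2 past Week 11 cure it?** Take the lead group at Week 11, just after the meeting. Their second injection, 12 weeks later (Section 6.3), falls at 11 + 12 = Week 23. The next listed meeting is Week 24. The second 40 µg dose would then precede every listed meeting held after any 40 µg exposure. The note under Table 1 lets first vaccinations move but does not say that the SMC dates move with them. Delay reconciles the text only if the later meetings shift too.

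**The case against.** The strongest case on the other side has four parts.

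**Section 3.3 does not conflict with SMC approval.** This stands. A reader might infer that Section 3.3 authorises 40 µg after four weeks without the committee. It does not: it sets a minimum interval, in a section about allocation and blinding, and it can apply together with Section 7.4.2. The defect is that no listed meeting can give the approval and that Section 3.3 does not state the condition.

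**Safeguards exist before Week 11.** This also stands. Two cohort 1 volunteers are injected a day ahead of the other 13, and five of cohort 2 go four weeks ahead of ten. Clinic visits fall on Days 3, 7, 14 and 28. The Medical Monitor may ask for an SMC meeting (Section 7.4.1), and the investigators must keep the SMC informed of new safety information. The Section 7.5 thresholds are low. A reader might infer that cohort 2 starts without oversight, and the protocol does not support that. But these safeguards act on events or perceived need and do not replace a planned approval. Criterion 5 of Section 7.5 requires a Grade 3 clinical event and exempts isolated Grade 3 local erythema or swelling. Several Grade 2 delayed local reactions in cohort 1 would trigger no automatic clinical hold.

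**The weeks are minimums and ad hoc meetings are allowed.** True, but neither a delay nor an ad hoc meeting is required. A reader might infer that starting after Week 11 satisfies everything with no further change, and Step 5 of the working shows that it does not.

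**The clause may be leftover text.** Sections 9.1.1 and 9.1.4 still refer to three doses and to nine controls at three per cohort, and the Week 36 meeting follows the last injection. A dropped third dose level would explain this, but that is inference. It would explain the inconsistency without removing it.

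**Conclusion.** The point holds as an internal inconsistency in the escalation gate. At minimum timing, 0 of the 3 listed SMC meetings precede the only escalation step, and all 15 first injections in cohort 2 (12 active) can be given before any scheduled review. An approval that Section 7.4.2 assigns to the SMC cannot operate as scheduled, and Section 3.3 does not state it as a condition.

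The conclusion rests on two readings. First, the previous cohort's last vaccination in Section 3.3 means the end of cohort 1's first round, which Table 1's Week 4 entry confirms. Second, cohort 2 starts at or near the minimum, which the 56-week duration implies.

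It does not extend to a claim that the trial lacks safety oversight. It should be settled before cohort 2 is dosed.

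**What to change.** Add to Table 1 and Section 3.3 an SMC review of cohort 1 safety data through the Day 28 visits, and state that SMC approval is required before the first 40 µg injection. With visits allowed to Day 33, this covers the full 10-28 day period for delayed reactions.

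The cost is a protocol amendment, one call of the existing committee and about one week. The 40 µg start moves 5 days past its Day 28 minimum plus the time for the call, to about Week 5. The remaining ten follow at about 5 + 4 = Week 9, and the last visit at about 9 + 48 = Week 57 instead of 56. The note under Table 1 already allows first vaccinations to move.

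Only if the sponsor confirms that a time-gated step was intended should the reference to dose escalation be deleted from Section 7.4.2 instead. The protocol should then say plainly that the 40 µg start depends on elapsed time and the Section 7.5 holds. That is a wording change with no effect on the schedule, but it gives up the planned review, so it is not an equal alternative.
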